## Abstract

**Background:**

Infancy and early childhood lay the foundation for language and reading abilities. They are crucial for success in social relationships, education, and work life, but can be compromised by heritable conditions such as developmental dyslexia. Music activities have shown associations with auditory, language, and literacy skills, but randomized controlled trials (RCTs) have been lacking, especially in young and at-risk populations. This two-arm RCT evaluates the efficacy of an early music intervention for language development. As highly novel aspects, we investigate whether and how the efficacy is influenced by familial dyslexia risk and its genetic markers, as well as intervention timing (children’s age and developmental status), and mediated by expected social–emotional benefits of the interventions on the parent, child, and their interaction.

**Methods:**

A maximum of 200 infants will be recruited for the trial, with approximately 50% of them at familial dyslexia risk, and randomized to the experimental (music intervention) or control arm (circus intervention), where they will start a weekly 6-month intervention at the age of approximately 8–12 months. Outcome measures will be evaluated at baseline, at 6 months (after the intervention), and at a 1-year follow-up (1.5 years from the baseline). As primary outcome measures of language development, language abilities will be evaluated with standardized parental questionnaires (validated parental report instruments) and neural speech processing with auditory event-related potentials. Further outcome measures include, for example, standardized tests of language development, standardized parental questionnaires on social–emotional factors, neural processing of music, questionnaires and standardized tests of motor development, and dyslexia genetics (DNA sampling).

**Discussion:**

The present trial is expected to fill significant gaps in previous research on the effects of early-age musical activities on language development. By comparing a musical intervention to an equally active, social, structured, and pleasurable circus intervention in a randomized, controlled setting with pre- and post-assessments, the unique benefits of musical activities can be probed reliably. The trial can provide completely novel information on the moderators and mediators of the intervention outcomes, including participant characteristics such as dyslexia risk, age, and developmental stage, as well as social–emotional benefits of pleasurable group activities.

**Clinical trial registration:**

ClinicalTrials.gov; identifier NCT06261307.

## Introduction

1

### Background

1.1

Infancy and early childhood lay the foundation for the fundamental human abilities of language and literacy (Kuhl, 2004). When language and literacy development are deficient or delayed, the risks of negative outcomes in later stages of life increase significantly, compromising school and career paths and possibly causing mental health issues. This raises the need for early interventions. A prevalent cause of atypical language and literacy development is developmental dyslexia (Eden et al., 2016; Peterson and Pennington, 2015), a specific learning disorder related to reading. Dyslexia is heritable, with several identified candidate genes affecting early brain development (Kere, 2014). Thus, infants born to dyslexic parents are an especially vulnerable group for deficient or delayed language and literacy development. While early support for language development is valuable for all children, these at-risk children are particularly in need of supportive and preventive interventions.

Dyslexia is understood to stem from a phonological processing deficit, associated with structural and functional abnormalities in the left auditory cortex, which is especially important for speech processing (Eden et al., 2016; Giraud and Ramus, 2013; Vellutino et al., 2004). Brain research, including electroencephalogram (EEG) studies utilizing the event-related potential (ERP) technique, has shown that neural auditory and speech processing problems in dyslexia (Hämäläinen et al., 2013) can be detected in infants at familial risk (Thiede et al., 2019; Virtala et al., 2022) and can also predict future problems in language and reading-related skills (Cantiani et al., 2016; Kailaheimo-Lönnqvist et al., 2020; Leppänen et al., 2010; Navarrete-Arroyo et al., 2024a; Navarrete-Arroyo et al., 2024b; see Volkmer and Schulte-Körne, 2018 for review). Thus, neural auditory and speech processing in infancy can be seen as a promising predictive marker for language and literacy development. Infancy is also an important sensitive period for the development of speech processing: it is a time of immense neural plasticity that helps the infant acquire the phoneme representations of the native language (Kuhl, 2004). Therefore, supporting auditory and speech processing early on could be a promising route to diminish the risk of later difficulties in language and literacy.

It is widely acknowledged that music-based interventions can have benefits for health and wellbeing across the lifespan [e.g., report by the World Health Organization (Fancourt and Finn, 2019)]. Specifically, music practice is positively associated with enhanced speech processing, language development, and literacy skills (Kraus and Chandrasekaran, 2010; Tallal and Gaab, 2006). These benefits are proposed to stem from the overlap between music and language, particularly their reliance on auditory (temporal) processing [for reviews and proposed frameworks, see (Fiveash et al., 2021; Ladányi et al., 2020; Patel, 2012; Peretz et al., 2015; Tierney and Kraus, 2014); meta-analysis (Neves et al., 2022)].

Furthermore, in infancy, many parent–infant interactions are naturally musical, and musical activities are recognized globally as part of early parenting (Trehub, 2019). This makes music particularly promising for infant interventions. In young, even preverbal children, correlational and intervention research shows that playful and informal musical activities, such as shared musical activities at home and musical playschool (early childhood music education), are associated with improved auditory and language skills (Linnavalli et al., 2018; Putkinen et al., 2019; Papadimitriou et al., 2021). Looking at intervention studies in typically developing infants, particularly active and social music interventions, compared to social activity with passive or no music exposure, have been shown to improve early language development (Gerry et al., 2012) as well as neural processing of speech and music (Zhao and Kuhl, 2016; see also Benasich et al., 2014; Musacchia et al., 2017; Zhao et al., 2022). However, these infant intervention studies often suffer from methodological weaknesses, making it uncertain if the obtained effects are attributable to the music activities (Virtala and Partanen, 2018, for review). To date, very few studies have incorporated both pre- and post-intervention assessments to demonstrate intervention-related change in outcome measures; furthermore, these studies rarely utilize several complementary assessment methods [such as neural and behavioral measures (Gerry et al., 2012; Trainor et al., 2012)]. Furthermore, aiming for large sample sizes is particularly important in infant intervention studies, given the high variability typically observed in infant behavioral and neurophysiological measures (Robb et al., 2018). So far, previous studies reviewed here report sample sizes of only around 20 per intervention group. Most importantly, the authors are aware of no previous music intervention studies on infants’ language development where music-making was compared to another equally structured group activity. This is required in order to probe the unique effects of music on early language development.

In terms of intervention timing, the previous active music interventions for infants have taken place around 6–12 months of age (Gerry et al., 2012; Zhao and Kuhl, 2016; Zhao et al., 2022; Trainor et al., 2012). This choice is justified, as infants younger than this have limited abilities for active participation, and the most sensitive period for phonetic learning is understood to end around 12 months (Kuhl, 2004). However, it is possible that a slightly later timing of a music intervention may result in additional or alternative benefits for language development. For example, infants around 12 to 18 months who have already uttered their first words and progressed in fine and gross motor development may be more ready to actively take part in music-making, such as singing, clapping, or instrument playing, than younger infants. Finding the optimal age for an early music intervention for language development would require the inclusion of infants at various ages in the same study.

Previous intervention studies comparing music-making to other structured group activities in older, school-aged children have shown benefits of music on reading and related skills (Chobert et al., 2014; Moreno et al., 2009), specifically in children with dyslexia (Flaugnacco et al., 2015; see also Habib et al., 2016; Moreno et al., 2015; Overy, 2000; Overy, 2003). However, research-based evidence is scarce on whether musical interventions for infants and young children at familial risk of dyslexia or language disorders could support auditory and speech processing, phonetic learning, and early language development, thus ameliorating later language and reading deficits. To this end, our recent pioneering intervention study in 0- to 6-month-old infants at familial risk for dyslexia showed benefits of vocal music listening on neural speech sound processing, including phoneme discrimination, compared to instrumental or no music listening (Virtala et al., 2023). The enhancement of speech–sound discrimination in the vocal music listening intervention group was observed as enhanced positive mismatch responses (MMRs), infant ERPs reflecting auditory discrimination abilities. However, group differences were no longer evident at 28 months of age (Virtala et al., 2023). This may be attributable to the passive nature of the music exposure, as musical interventions that include active participation and social interaction seem to result in greater benefits, as reviewed above. Investigating their potential benefits in these at-risk groups calls for more research, as inherited risk factors may significantly moderate intervention outcomes. This could help in effectively targeting interventions to those children who can truly benefit from them.

In addition to enhanced auditory and language abilities, active and social music-making improves social–emotional development in infants and children (Gerry et al., 2012; Kirschner and Tomasello, 2010) and can support parent–infant interaction and parental wellbeing (Kostilainen et al., 2021). These broad social–emotional benefits of musical interventions are closely tied to the rewarding nature of music (Salimpoor et al., 2015) and might act as important mediators between musical activities and enhanced language development. However, these benefits are not unique to musical interventions and may also be achieved by other pleasurable group activities promoting social interaction. These benefits should thus be taken into account as potential mediators when evaluating the efficacy of both music and active control interventions on language development. Furthermore, ideally, the music and active control interventions should be at least somewhat balanced in their level and quality of social interaction. For example, in studies of older children, music interventions have often been compared with painting or visual arts (Flaugnacco et al., 2015). If the painting lessons contain less social interaction than the music lessons, this difference itself can contribute to the obtained benefits of music lessons for language and literacy.

To this end, based on the evidence presented above, we argue that active, social music-making in infancy and early childhood will result in improved language development through factors specific to music activities and by factors more generally important for early learning. The factors specific to music activities include particularly exposure to and (synchronous) production of musical and speech sounds, such as rhythms, melodies, rhymes, and singing. These result in (1) improved auditory/temporal processing as postulated, e.g., in Fiveash et al. (2021), but also (2) improved phonetic learning [as shown in Virtala et al. (2023)] that will benefit language development due to shared neural mechanisms. The more general factors important for early learning include the social setting and the pleasurable sensory–motor activity and stimulation, these two being also heavily intertwined and supported by the presence of the primary caretaker. Thus, we state that music intervention studies should introduce an active control intervention that shares these general factors enabling early learning while lacking the factors specific to music activities. This way, the studies can reliably probe whether music activities can have specific benefits on early language development over the benefits achieved by any structured social, pleasurable, and age-appropriate activity.

### Objectives and research questions

1.2

The present study aims to fill important research gaps by investigating the effectiveness of an active, social music intervention compared to an equally active and social non-musical intervention (circus) for early language development. The participants will be infants ranging from eight to 12 months at the start of the intervention, with or without familial dyslexia risk. This will allow us to investigate how the infants’ age and developmental stage, as well as their familial risk factors, affect potential intervention outcomes. The comparators (intervention arms) were chosen and designed so that both are structured, social, and pleasurable, targeting important aspects of early development. Both activities are established and popular parent–infant hobbies in Finland and are therefore expected to be well-suited for the age group. The choice of family circus as an active comparator is supported by a recent scoping review concluding that circus interventions consisting of activities such as acrobatics, balancing, and juggling can benefit physical/motor and social–emotional development (Coulston et al., 2023). Thus, while the music and circus interventions share the general aims of promoting early learning and social interaction, they differ in their arm-specific aims (promoting musical vs. motor abilities, respectively). Language development is assessed with complementary behavioral and neural measures, namely standardized parental questionnaires (validated parental report instruments), tests on language abilities, and ERPs and MMRs to speech sounds and their changes.

As highly novel aspects, this trial aims to investigate how the intervention effects are modified by the participants’ age and developmental stage, as well as their inherited risk factors (i.e., familial dyslexia risk). It is further evaluated whether and how intervention arms differ in their social–emotional benefits and how the intervention benefits on language are mediated by the social–emotional benefits. These objectives are investigated in the following five main research questions (with relevant hypotheses referred to in parentheses):

*R1:* What are the effects of a social and active music intervention vs. a similar non-musical (control) intervention in infancy on language development (H1, H2)?

*R2:* How are the intervention effects in R1 influenced by the timing of the intervention (child’s age and developmental status, especially related to language and motor skills; H3)?

*R3:* How are the intervention effects in R1 modified by familial dyslexia risk (H4)?

*R4:* Are intervention effects in R1 mediated by the social–emotional benefits of the interventions, including infants’ social–emotional development, parental wellbeing, and parent–infant interaction (H5)?

*R5:* Do the two intervention arms have specific benefits on the abilities that are targeted directly (music processing in the music intervention, H6; motor abilities in the circus intervention, H7)?^1^

### Trial design and hypotheses

1.3

This randomized controlled trial is conducted as a double-blind, two-arm parallel assignment design with the primary purpose of treatment, with primary and secondary outcomes assessed at baseline, post-intervention, and at follow-up approximately 1.5 years from baseline. The experimental arm will receive family music training (music intervention), and the control arm will receive family circus training (circus intervention). The study framework is a superiority trial with greater expected benefits from the experimental than the control arm. All participants are randomized to one of two interventions with a 50:50 allocation ratio, both consisting of approximately 6 months of weekly group sessions together with a parent (Figure 1: study flowchart).

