#### Participant recruitment and consent

2.1.1

The participants are infants from Finnish families from the greater Helsinki region, recruited between March 2024 and September 2025 by distributing paper flyers and digital advertisements via the project website, social media (Facebook, Instagram), local maternity clinics, and public events and lectures. Families can express their interest in participation via an electronic form on the project website or by contacting the trial coordinator via the project email. Participation is expected to be appealing to families due to the intervention, which is offered at no cost to all participating families and is similar to a self-paid infant–parent hobby. In order to achieve a sufficient sample size (see 2.1.3), recruitment will continue for approximately 1.5 years.

The trial coordinator screens the families for eligibility and the need for parental dyslexia testing (see 2.1.2) on the phone with the parent and, after receiving oral consent for participation from the parent, conducts stratification, randomization, and allocation of eligible infants to the two intervention arms (see 2.2).

One or both parents of the infant will be provided with a participant information sheet and data protection notice and will sign written informed consent for participation before starting the baseline assessment. This study is conducted at the University of Helsinki, Finland. The study has been approved by The University of Helsinki Research Ethics Committee in the Humanities and Social and Behavioral Sciences with the title “Infant and toddler age hobbies as support for language development (BusyBaby)” (public title translated from Finnish), and preregistered at ClinicalTrials.gov with the title “Language Development Deficits and Early Interactive Music Intervention—a Randomized Controlled Trial (BusyBaby)” (scientific title; NCT06261307, February 7th, 2024). Any important protocol modifications will be reported at the preregistration site.

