Blindness of the researchers to the randomization has been ensured by assigning a dedicated member of the research team as trial coordinator. The trial coordinator screens participants for eligibility and assigns them to the two intervention arms according to the randomization sequence. When the evaluation of dyslexia risk has to be conducted, the trial coordinator will assign the evaluation to one of the outcome assessors, and that assessor will not participate in future outcome assessments for that family (as their blindness to the participant’s dyslexia risk status has been violated). The trial coordinator will not act as an outcome assessor or intervention instructor and will keep track of any blindness violations.

Blindness of the participants to the trial design is ensured by presenting the study as evaluating the effect of early-age hobbies on language development, without either intervention being a control arm. To evaluate how successful this was, participating families are queried about their expectations regarding the benefits of the two intervention arms on the primary outcome measures (see Supplementary material).

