#### The experimental arm (music intervention)

2.3.1

The music intervention is planned based on the practices of Finnish early childhood music education and consists of social, structured, and playful group sessions that involve joint singing, playing with musical instruments, and moving to and listening to music. Based on common age-appropriate practices of Finnish early childhood music education, rhythmic exercises such as tapping, clapping, and playing percussion instruments (claves, maracas, etc.) with infants and parents together, as well as joint singing (mostly by parents), are emphasized in the sessions. Their use is supported by previous research, for example, on the benefits of rhythmic exercises on literacy in dyslexic children (Flaugnacco et al., 2015) and on the benefits of vocal music exposure on speech processing (Virtala et al., 2023). The arm-specific aim is to support the development of musical abilities.

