### Risk assessment and monitoring

2.8

Participation in the interventions is expected to have no adverse effects on the health, wellbeing, or safety of the participating families. Therefore, a data monitoring committee has not been appointed. Nevertheless, intervention instructors are asked to report all negative occurrences in their intervention groups after each session, including, for example, minor accidents, crying or negative emotions, and conflicts between the participants (see Supplementary material). Additionally, all negative feedback or concerns raised by the parents that the intervention instructors, researchers, outcome assessors, or trial coordinator receive during the trial will be collected and stored by the trial coordinator.

Challenges in participant recruitment or attrition are expected to be minor, particularly regarding the primary outcomes (evaluated directly before and after the intervention) for three main reasons. Firstly, participation in the trial is expected to be engaging and rewarding, as pointed out in section 2.1.3. Secondly, several actions are taken to support adherence and commitment to the study, as described in section 2.4. Thirdly, the follow-up period of 1.5 years in total is considered relatively short. Challenges related to data loss are further minimized by using complementary outcome measures. For example, while EEG recordings may not always be successful in infancy and early childhood due to movement artifacts and participant refusal, parental questionnaires will still provide valuable information. Nevertheless, participant drop-outs and no-shows are carefully monitored (see also Supplementary material).

The following measures have been taken to ensure intervention fidelity and arm equivalence. The interventions have been planned in advance, and their execution is based on detailed lesson plans. Teachers are asked to report any deviations from the lesson plan or duration after each lesson. The teachers have planned the lessons together and meet regularly (1 h/month) during the interventions to harmonize their practices as much as possible. The authors PV and BA conduct lesson observations for all teachers. For more information, see Supplementary material.

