It is important to note that the 4-month age range of the participants will introduce considerable variation in the baseline and post-intervention outcome measures, making it more challenging to obtain significant intervention effects, especially if the benefits are small. However, participant allocation to the intervention arms is done so that the mean age remains similar in the two arms. The age range was also agreed upon with the intervention instructors to ensure that it would not compromise the practical implementation of the interventions, i.e., that children at both ends of the age range would be able to participate in the lessons in a meaningful way with the help of their parents. While participant age intentionally varies in the present trial, intervention intensity and duration are fixed to one weekly lesson for approximately six months. Therefore, evaluating the optimal intensity and duration for this kind of intervention is beyond the scope of this trial.

Due to the young age of the participants at baseline, the assessment of language abilities is based solely on parental questionnaires (validated parental report instruments). This is not optimal for the reliability of the language assessment and may particularly affect the evaluations of dyslexia-risk infants, as their dyslexic parents may struggle with correctly completing the long questionnaires. A standardized language test battery will be additionally administered at the post-intervention and follow-up assessments. Correlating its results with those of the parental questionnaires will increase the reliability of the obtained effects.

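### The trial is called double-blind, but parents know their arm and supply both language-ability primary outcomes, so a questionnaire-only gain could partly reflect reporting that differs by arm

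*Protocol article*

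**What the plan says.** Section 1.3 (Trial design and hypotheses) describes the trial as "conducted as a double-blind, two-arm parallel assignment design". The same section says that both arms receive "weekly group sessions together with a parent". Section 2.3.1 adds that parents do most of the singing in the music arm.

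Section 2.2 explains what participant blinding means here: "Blindness of the participants to the trial design is ensured by presenting the study as evaluating the effect of early-age hobbies on language development", with neither arm presented as the control. Families are asked what benefits they expect from each arm, so that the success of this masking can be judged. The Discussion (section 3) repeats the double-blind aim in the same sense and expects it to minimise the effect of participants' motivation and expectations on the primary outcomes.

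The primary outcomes (2.5.1) are two parental report instruments, the CSBS ITC and the FinCDI-LF, and speech ERPs and MMRs from EEG. Of the baseline visit, section 3.1 (Limitations) says that "the assessment of language abilities is based solely on parental questionnaires". The assessor-administered RDLS-III (2.5.2.1) is secondary, has no baseline, and is given at post-intervention to children below its age range.

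On the research team, section 2.2 states: "Blindness of the researchers to the randomization has been ensured by assigning a dedicated member of the research team as trial coordinator". Elsewhere, one investigator is said to have generated the randomization sequence (2.2), to supervise the outcome assessors (2.5) and to have access to the allocation files as a safeguard (2.7). Section 2.8 says that this investigator and a second author "conduct lesson observations for all teachers".

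**The concern.** Double-blind normally tells a reader that neither the participant nor the person supplying the outcome knows the allocation. Here the parent takes part in the intervention and is also the rater for one of the two kinds of primary outcome. What the article describes is masking to the hypothesis, which is weaker.

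H1 predicts a larger questionnaire gain in the music arm. If parents in a music class expect more for language than parents in a circus class, and rate accordingly, the arm-by-time interaction would move in the direction of H1 without any change in the children. Section 3.1 discusses the reliability of parent report and dyslexic parents' difficulty with long forms. It does not mention reporting that differs by arm, and section 3 relies on the blinding label to discount expectation effects. A reader would therefore take a questionnaire gain as better protected than it is.

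The statement about the researchers matters for the EEG outcome. ERP latencies and amplitudes depend on processing choices, so their protection rests on who makes those choices and what that person knows.

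**Working it through.** **1. Who knows what.**
- *Parent:* attends the sessions (1.3), so knows the activity; is told that the study is about hobbies and language (2.2); completes both language-ability primaries (2.5.1.1). Aware of arm; at most unaware of which arm is favoured.
- *Outcome assessors:* the coordinator who holds the allocation does not assess (2.2); allocation files are open only to the coordinator and one investigator, and allocation is stored in the databases so that it is not revealed by accident (2.7). Nothing shows that assessors are unblinded.
- *One investigator:* sequence (2.2), supervision of assessors (2.5), allocation files (2.7), lesson observation (2.8). Blindness is not ensured for this role.

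**2. Variance model, checked against the plan's own figure.** Inputs from 2.1.3: effect 0.31 SD, correlation 0.7, alpha 0.05 (sidedness not stated; two-sided taken), power 0.80.
- SD of change = √(2 × (1 − 0.7)) = √0.6 = 0.775.
- n per arm = 2 × 0.6 × (1.960 + 0.842)² / 0.31² ≈ 98.0, rounded up to 99.
- Section 2.1.3 gives 100 per arm from simulation for the arm-by-time interaction in the mixed models. The model reproduces this closely enough to use.

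**3. Effect of an assumed reporting differential b when the true effect is zero.** The documents give no value of b; 0.10, 0.15 and 0.20 SD are assumptions. They equal 32%, 48% and 65% of the planned 0.31.
- SE = 0.775 × √(2/n).
- P(reject) = Φ(b/SE − 1.96) + Φ(−b/SE − 1.96).
- n = 77 is half of the 154 infants with a baseline assessment (2.6; actual split 75 and 79). SE = 0.125.
- n = 62 applies the maximum 20% loss in 2.1.3: 154 × 0.8 / 2 = 61.6. SE = 0.139.

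| Assumed b (SD) | b/SE at 77 | P(reject) at 77 | b/SE at 62 | P(reject) at 62 |
|---|---|---|---|---|
| 0 | 0 | 5% | 0 | 5% |
| 0.10 | 0.80 | 13% | 0.72 | 11% |
| 0.15 | 1.20 | 22% | 1.08 | 19% |
| 0.20 | 1.60 | 36% | 1.44 | 30% |

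**4. Observed difference that just reaches p = 0.05.** 1.96 × SE is about 0.24 SD at 77 per arm and 0.27 SD at 62 per arm. Both are below the planned 0.31, so a differential smaller than the target effect could by itself produce a significant result.

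These figures are for one unadjusted questionnaire test. Section 2.9 promises multiplicity adjustment, which would lower them.

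**The case against.** Parents cannot be blinded in any class-based intervention. The article states its narrower meaning of blinding in both 2.2 and 3. The comparator is active and equally social, which is a real strength. Expectations about both arms are collected. Section 3.1 already lists reliance on parent report as a limitation, and the ERP/MMR primary is not parent-reported. All of this stands. It confines the problem to a gain on the questionnaires that the ERPs and MMRs do not share, but does not remove it. Correlating the questionnaires with the RDLS-III, as 3.1 proposes, would not remove a bias that differs by arm.

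Four stronger readings are tempting and should not be drawn.
- *Assessors or EEG analysts are unblinded.* The documents do not say so. Section 2.5 has the investigator supervising assessors, not scoring outcomes; 2.7 describes the access to allocation files as a safety procedure; and writing a permuted list does not in itself reveal a family's arm.
- *Families can read the hypothesis in the study title.* Section 2.1.1 calls the title that names music the scientific title and gives a neutral public title. Nothing shows which title families see.
- *The questionnaire results will be biased.* The direction is plausible, but neither direction nor size is shown.
- *Efficacy should be claimed only if the ERPs or the follow-up RDLS-III point the same way.* Agreement in sign is undefined across several ERP measures and filters little. With no effect and independent signs, at least one of the two agrees 75% of the time (1 − 0.5 × 0.5), so 36% would fall only to 27%.

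The supplement is not shown, and it or the full plan may say how the expectation ratings are analysed and how the EEG is processed. Silence on those details is therefore not counted as an error.

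**Conclusion.** The concern holds in this form. The double-blind label in 1.3 and 3 claims a property that the design does not have for the people who supply both language-ability primaries. The claim in 2.2 about researchers is broader than 2.5, 2.7 and 2.8 support. A gain confined to the questionnaires could partly reflect arm-aware reporting, and the article does not list that as a limitation.

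How much this matters depends on assumed bias. On the plan's own variance assumptions, 0.10 to 0.20 SD of differential reporting would raise a 5% error to between 13% and 36% at 77 per arm, or between 11% and 30% at 62 per arm, for a single unadjusted two-sided test. The ERP/MMR primary is not exposed to this route. The label and the interpretation should be corrected; the design itself need not change.

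**What to change.** 1. In 1.3 and 3, replace 'double-blind' with 'outcome assessors blind to arm; parents aware of arm but not told which arm is the control'. In 2.2, limit the claim of ensured blindness to the outcome assessors.
2. In 3.1, add that the language-ability primaries are reported by parents who know their arm.
3. State before the analysis that a questionnaire gain without a matching ERP/MMR effect is reported as a parent-reported difference, not as established language efficacy. Name in advance the ERP/MMR contrast that counts as matching.
4. Add a sensitivity analysis of the questionnaire primaries using the expectation ratings already collected.
5. Complete EEG processing and peak extraction on arm-masked files, without input from anyone who has observed lessons or can open the allocation files.

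The cost is a more modest blinding claim, one added analysis and a working rule for the EEG files. No new data are needed.
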